## Abstract

**Background:**

Astronauts have a higher risk of cervical intervertebral disc herniation. Several mechanisms have been attributed as causative factors for this increased risk. However, most of the previous studies have examined potential causal factors for lumbar intervertebral disc herniation only. Hence, we aim to conduct a study to identify the various changes in the cervical spine that lead to an increased risk of cervical disc herniation after spaceflight.

**Methods:**

A cohort study with astronauts will be conducted. The data collection will involve four main components: a) Magnetic resonance imaging (MRI); b) cervical 3D kinematics; c) an Integrated Protocol consisting of maximal and submaximal voluntary contractions of the neck muscles, endurance testing of the neck muscles, neck muscle fatigue testing and questionnaires; and d) dual energy X-ray absorptiometry (DXA) examination. Measurements will be conducted at several time points before and after astronauts visit the International Space Station. The main outcomes of interest are adaptations in the cervical discs, muscles and bones.

**Discussion:**

Astronauts are at higher risk of cervical disc herniation, but contributing factors remain unclear. The results of this study will inform future preventive measures for astronauts and will also contribute to the understanding of intervertebral disc herniation risk in the cervical spine for people on Earth. In addition, we anticipate deeper insight into the aetiology of neck pain with this research project.

**Trial registration:**

German Clinical Trials Register, DRKS00026777. Registered on 08 October 2021.

**Supplementary Information:**

The online version contains supplementary material available at 10.1186/s12891-022-05684-0.

## Background

Astronauts have a markedly increased risk of cervical and lumbar intervertebral disc (IVD) herniation after spaceflight [1]. A review of the literature [2] suggested that hyperhydration of the lumbar IVDs during spaceflight is the most probable mechanism for increased lumbar IVD herniation risk post-flight. However, it is not clear whether this is a mechanism occurring within the cervical spine. Further, recent data on the lumbar spine [3, 4] did not reveal increased IVD hydration post-flight, and rather suggested that muscle atrophy may be a potential cause. Hyperhydration of the cervical IVDs may occur during spaceflight, as observed in short-term recumbency [5], but there is no data on this yet.

Beyond IVD hydration, several other factors could influence the injury risk of the cervical spinal tissues, including the discs. For example, muscle function as well as neurovestibular function are known to be impaired after spaceflight, which can impede the control of the neck muscles [6–13]. Data from people with neck pain has revealed that the deep cervical extensors (i.e. suboccipital muscles, m. semispinalis cervicis and multifidus muscle) [14] and deep cervical flexors (i.e. longus colli and capitis) [15] commonly show reduced activation in the presence of pain. However, these muscle groups have not yet been examined in astronauts in any detail. Furthermore, studies [16–18] in patients with neck pain have demonstrated the presence of fat infiltration and pseudohypertrophy of the musculature, which may mask muscle atrophy, and could be an indicator of muscle dysfunction itself.

Further, adaptations of the cervical IVD occurring during spaceflight may be accompanied by changes in the adjacent vertebral bodies and end-plates. The IVD receives its nutrition via the end-plates [19], and end-plate damage is suggested to lead to IVD degeneration [20, 21]. Furthermore, with bone loss of the vertebrae, as in persons with osteoporosis, the (lumbar) IVDs are affected and increase in size [22]. If bone loss occurs in the cervical spine, this may result in deformation of the vertebral end-plate, reduced loads on the disc, and hence could impact disc hydration.

To date, as identified in a prior review [2], there has been no systematic examination of cervical spine adaptations due to weightlessness. Prior ground-based research in prolonged bed-rest [23] indicated that prolonged bed-rest is likely an inadequate model to simulate the effects of spaceflight on the cervical spine.

The aim of this study is therefore to examine potential factors associated with cervical IVD herniations before and after spaceflight. Our a priori hypotheses were that the following will be observed after spaceflight.Increases in cervical disc volumeIncreases in cervical disc hydrationReduced muscle oxygenation and blood flow in the cervical regionThe deep cervical extensor muscles (i.e. suboccipital muscles, m. semispinalis cervicis and multifidus muscle) and the deep cervical flexors (i.e. m. longus colli and capitis) will undergo atrophyAn increase in neck muscle fat contentReduced range of cervical spine movementsReduced speed of cervical spine movementsAberrant motions, defined as when the instantaneous helical axis folds back upon itself and movement is not continued anymore, will occur more frequentlyReduced endurance capacity of the neck musclesDecreased neck flexor and extensor maximal strengthNeck muscle activity will be decreased during maximal and sustained isometric contractionsNeck flexor-extensor co-activation will increase (during isometric and maximal contractions)A more homogenous pattern of spatial motor unit activityIncreased motor unit discharge rate variability and force tremor (reduced force steadiness)Decreased motor unit conduction velocity in the neck musclesCervical spine bone density will decreaseIncreases in cervical disc volume will lead to increased stress and strains in cervical spines during loading upon return to EarthIncreases in cervical disc volume will lead to increased risk of disc herniations

## Methods

This cohort study will include astronauts who have stayed at the International Space Station (ISS) in order to identify the factors involved in spinal dysfunction and cervical IVD herniation. We will not include pregnant women, subjects that have non-MRI compatible metal implants, or electronic implants. It will be conducted as a multi-center study at the Johnson Space Center, Houston (Texas); European Astronaut Centre, Cologne (Germany) and the University of Texas Medical Branch, Houston (Texas). The planned protocol is in accordance with the Helsinki Declaration of ethical principles [24] and approved by the NASA (Study000000222, NASA MPA Number NASA7116301606HR) and ESA (ILSRA-2014-0033) Institutional Review Board. This study was prospectively registered in the German Clinical Trials Register (Approved on 08 October 2021, registration number DRKS00026777). The STROBE checklist (Supplementary material 1) was used to report the components for this study protocol [25].

The planned investigation will be presented to the crew members by the science team members ([name], GA) in an Informed Consent Briefing (ICB) of the NASA Human Research Program. Additionally, a video ICB illustrating all required science and operational aspects of the study will be prepared. After the ICB, the crew members have 3–4 weeks to express their interest in participating in the presented study. A written informed consent will be obtained from the participants.

The number of astronauts a research group can recruit for measurements is always limited. Using data from an earlier study [23], we calculated test-retest repeatability of average cervical disc volume (average of all discs from C2/3 to C7/T1) with 1.5 years between testing sessions. We observed a correlation of 0.964 (95% CI: 0.913–0.986) between measures on the same 21 participants separated by 1.5 years. The mean (SD) average cervical disc volume was 2.01(0.31) cm^3^. If 10 astronauts are to be measured, pre- and post-flight, and given the above repeatability data, the calculated detectable effect size would be a 2.07% difference (95%CI: 1.31–3.24%) in average cervical disc volume before and after spaceflight. This assumed a repeated measures ANOVA design and testing for within-factor (i.e. pre-flight vs. post-flight) differences with an alpha-level of 0.05 and a power of 0.80. These calculations were performed in G*Power3 version 3.1.2 [26, 27].

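### The detectable pre–post difference in disc volume is printed as 2.07%, but the article's own inputs give about 4.1%, twice as large

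*Protocol article*

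**What the plan says.** The sample-size paragraph in the Methods section of the protocol article supplies everything needed to check its result.

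- Number of astronauts and occasions: "If 10 astronauts are to be measured, pre- and post-flight, and given the above repeatability data".
- Repeatability: "We observed a correlation of 0.964 (95% CI: 0.913–0.986) between measures on the same 21 participants separated by 1.5 years".
- Location and spread, in cm³: "The mean (SD) average cervical disc volume was 2.01(0.31) cm".
- Model: "This assumed a repeated measures ANOVA design and testing for within-factor (i.e. pre-flight vs. post-flight) differences". The significance level is set at 0.05 and the power at 80%.
- Software: "These calculations were performed in G*Power3 version 3.1.2".
- Result: "the calculated detectable effect size would be a 2.07% difference (95%CI: 1.31–3.24%) in average cervical disc volume before and after spaceflight".

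No other power or sensitivity statement appears in the article. Increased disc volume is the first hypothesis listed in the Background, and the last two listed hypotheses build on it.

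**The concern.** A within-subject factor with two levels is the same test as a two-sided paired t-test, so the detectable difference can be checked by hand. With 10 pairs, 80% power needs a mean change of about one SD of the differences. The stated correlation and SD put that SD at about 0.083 cm³, roughly 4% of the mean. A figure near 2% is therefore too small by a factor of about two.

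The figure matters because the number of astronauts is limited. When the sample cannot easily grow, the detectable difference is the main guide to reading a null result. As printed, it suggests that a non-significant finding makes a change of 2% or more unlikely, when the design would miss a 2% change more often than not.

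**Working it through.** **Inputs** (all from the sample-size paragraph in Methods): n = 10 pairs; r = 0.964, limits 0.913 and 0.986; SD = 0.31 cm³, taken as equal on both occasions; mean = 2.01 cm³; α = 0.05; power = 0.80.

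**Step 1. Required standardised paired difference.** The test statistic follows a noncentral F with 1 and 9 degrees of freedom and noncentrality λ = n·dz². The critical value is 5.117. Solving for 80% power gives λ = 9.92, so dz = √(9.92/10) = 0.996.

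**Step 2. Reproducing the printed figure.** G*Power's repeated-measures module uses λ = f²·n·m/(1 − r) with m = 2 occasions. Setting the two expressions for λ equal gives f = dz·√((1 − r)/2). Multiplying by SD/mean = 0.31/2.01 = 0.1542:

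| r | f | f·SD/mean | Printed |
|---|---|---|---|
| 0.964 | 0.1336 | 2.06% | 2.07% |
| 0.913 | 0.2077 | 3.20% | 3.24% |
| 0.986 | 0.0833 | 1.29% | 1.31% |

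The remaining gaps are of rounding size. Taking f as 0.134 gives 0.134 × 0.1542 = 2.07%, and f as 0.21 gives 3.24%. For the lower limit, an unrounded r of 0.9855 gives f = 0.996 × √(0.0145/2) = 0.0848 and 1.31%. The three printed values therefore correspond to f·SD/mean.

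**Step 3. The correct conversion.** Cohen's f is the SD of the group means about their grand mean, divided by the within-occasion SD. With two means each lies half the difference from the grand mean, so f = |difference|/(2·SD) and the difference is 2·f·SD.

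**Step 4. Cross-check by the paired route, without f.** SD of the difference = SD·√(2(1 − r)); detectable difference = 0.996 × that SD.

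| r | SD of difference (cm³) | Detectable difference (cm³) | As % of 2.01 | Printed |
|---|---|---|---|---|
| 0.964 | 0.31·√0.072 = 0.0832 | 0.0828 | 4.12% | 2.07% |
| 0.913 | 0.31·√0.174 = 0.1293 | 0.1288 | 6.41% | 3.24% |
| 0.986 | 0.31·√0.028 = 0.0519 | 0.0517 | 2.57% | 1.31% |

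This agrees with 2·f·SD/mean in every row.

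**Step 5. What 2.07% delivers.** A 2.07% change is 0.0207 × 2.01 = 0.0416 cm³. At r = 0.964 this is dz = 0.0416/0.0832 = 0.50, and power with 10 pairs is 29%. At r = 0.913 it is 15%, and at r = 0.986 it is 62%. At r = 0.964, 34 pairs are needed for 80% power.

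**Step 6. Can another reading give 2.07%?**

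- One-sided paired test, n = 10: 3.53%.
- Normal approximation, n = 10: 3.67%.
- Twenty pairs, two-sided: 2.73%.
- Rounding of r (0.9635 to 0.9645) and SD (0.305 to 0.315) together: the correct value stays between 4.03% and 4.22%.
- Solving for the r that makes 2.07% correct with n = 10 gives about 0.991, above the article's own upper limit of 0.986.

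None of these reproduces the printed figure.

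**The case against.** The arithmetic itself is not open to serious dispute. The objections concern what follows from it.

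- **The sample size was not derived from 2.07%.** The paragraph opens by noting that astronaut numbers are always limited and then asks what 10 could show. This stands: the error affects the stated sensitivity, not the planned number, and the figure of 34 astronauts shows scale only.
- **Nothing in the plan depends on 2.07%.** It sets no equivalence margin or decision rule, and disc volume is one of 18 listed hypotheses with none singled out as primary. This also stands and limits the consequences, but a printed power claim should still be true.
- **The cause is inferred.** The article does not show how it converted the G*Power output. That is correct. The match at all three values makes the explanation very likely, but the factor of two follows from the stated inputs whatever the cause.
- **The study has several time points.** The abstract plans repeated sessions before and after flight. If two scans on each side were averaged and their errors were independent (an assumption), the detectable difference would fall to about 4.12%/√2 = 2.9%. That is still above 2.07%, and it is not the calculation the article describes, which compares pre-flight with post-flight as a two-level factor.
- **The correlation may not carry over.** It comes from repeat testing 1.5 years apart in an earlier study, not from spaceflight. Variation between astronauts in their response to flight would raise the detectable difference; a shorter interval between sessions might lower it. The article cannot settle the net direction, so 4.1% should be tied to its stated assumptions rather than called a best or worst case.

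**Conclusion.** The concern holds. On the article's own inputs the detectable pre–post difference is 4.1% (0.083 cm³), ranging from 2.6% to 6.4% over the confidence interval of the correlation. The printed point value and both limits are about half of these, and the error makes the study look more sensitive than it is.

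This rests on one pre-flight and one post-flight value per astronaut, equal SDs of 0.31 cm³ on both occasions, complete data on 10 astronauts, and a two-sided test at an unadjusted 0.05. The false discovery rate control planned under Statistical analysis would, if anything, reduce power further.

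**What to change.** Restate the result in the sample-size paragraph along these lines: with 10 astronauts, one measurement before and one after flight, α = 0.05 and 80% power, the detectable difference in average cervical disc volume is about 4.1% (0.083 cm³), or 2.6% to 6.4% over the 95% confidence interval of the repeat correlation. Add that a non-significant result will not be read as excluding changes smaller than this.

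The authors should also check the conversion from the G*Power output in their own files, since the cause given here is inferred.

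The cost is one sentence and a less favourable figure. Enrolment, measurements and the planned analysis stay as they are.

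### The detectable disc-volume change of 2.07% (1.31–3.24%) has an interval built from the correlation alone and a centre half of what the stated inputs give; both need correcting together

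*Protocol article*

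**What the plan says.** The relevant text is the sample-size paragraph in Methods of the protocol article. It takes its repeatability data from an earlier study: "We observed a correlation of 0.964 (95% CI: 0.913–0.986) between measures on the same 21 participants separated by 1.5 years". It adds: "The mean (SD) average cervical disc volume was 2.01(0.31) cm^3". The design premise is "If 10 astronauts are to be measured, pre- and post-flight", and the calculation is described as follows: "This assumed a repeated measures ANOVA design and testing for within-factor (i.e. pre-flight vs. post-flight) differences". The significance level is 0.05 and the power 0.80. The software is named: "These calculations were performed in G*Power3 version 3.1.2". The result is that "the calculated detectable effect size would be a 2.07% difference (95%CI: 1.31–3.24%) in average cervical disc volume".

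The paragraph does not say how the interval was obtained. It gives no SD of the paired differences and no uncertainty for the SD of 0.31 cm³.

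**The concern.** The interval is labelled a 95% CI, and it is the article's only statement of how uncertain its detectable difference is. Its relative width matches what results when only the correlation is varied. In a sample of pairs, the estimated correlation and the estimated between-person SD move together. A more heterogeneous sample raises both, and the effect largely cancels in the SD of the differences, which is all that the pre/post test uses. Varying one and freezing the other counts between-person sampling error that the test never sees.

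The centre of the interval also does not follow from the stated inputs as a pre/post difference, so its position has to be checked as well as its width.

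What is at stake is the interpretation of the disc-volume result, which is the first hypothesis listed. A reader would take changes of 1.3% to 3.2% as the plausible limit of detection. A non-significant result could then be read as excluding changes that the study has little power to see.

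**Working it through.** **Inputs (all from the sample-size paragraph).** n = 10 astronauts; r = 0.964 (0.913–0.986) from 21 pairs; mean 2.01 cm³; SD 0.31 cm³; alpha 0.05; power 0.80; one group, two time points.

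**1. Reproducing the point value.** For an F test with 1 and 9 df, alpha 0.05 and power 0.80, the required noncentrality is λ = 9.920. For a within-factor with two levels, λ = 2n·f²/(1 − r), so

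f = √(λ(1 − r)/(2n)) = √(9.920 × 0.036/20) = 0.1336.

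Then f × SD/mean = 0.1336 × 0.31/2.01 = 2.06%, against 2.07% printed. Rounding of r, SD and mean allows 2.01–2.11%, so the printed value is reproduced.

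**2. What that number is.** With two time points, f = δ/(2·SD), where δ is the pre/post difference. Hence δ = 2·f·SD, and f × SD/mean is half of the detectable difference. The paired calculation confirms it:

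- SD of differences = 0.31 × √(2 × 0.036) = 0.0832 cm³
- standardised difference needed = √(9.920/10) = 0.996
- δ = 0.996 × 0.0832 = 0.0828 cm³, and 0.0828/2.01 = 4.12%

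A one-sided test (3.53%) or a two-sided normal approximation (3.67%) does not give 2.07% either.

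**3. Reproducing the interval.** The Fisher-z limits of r are tanh(atanh(0.964) ± 1.96/√18) = 0.9117 and 0.9856. (An unrounded r of about 0.9644 gives limits that round to the printed 0.913 and 0.986.) With the SD fixed, the detectable difference scales with √(1 − r):

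- 2.07 × √((1 − 0.9117)/0.036) = 3.24%
- 2.07 × √((1 − 0.9856)/0.036) = 1.31%

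Both match the printed limits.

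**4. The interval that 21 pairs support.** The SD of 21 paired differences has 20 df. The chi-square quantiles are 34.17 and 9.59, so the 95% limit factors are √(20/34.17) = 0.765 and √(20/9.59) = 1.444. The printed factors are 1.31/2.07 = 0.633 and 3.24/2.07 = 1.565.

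- On the printed centre: 2.07 × 0.765 to 2.07 × 1.444 = 1.58–2.99%, width 1.41 points against 1.93 printed. Ratio 1.37.
- On the log scale: ln(3.24/1.31) = 0.906 against ln(1.444/0.765) = 0.635. Ratio 1.43 (1.425 unrounded), or 42% averaged over simulated samples.
- On the paired centre: 4.12 × 0.765 to 4.12 × 1.444 = 3.15–5.95%, width 2.80 points.

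**5. Coverage.** In 100,000 simulated samples of 21 bivariate normal pairs with correlation 0.964, the correlation-only recipe, applied to the SD of the differences, covered the true value 98.6% of the time. The chi-square interval covered 94.8%.

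**6. Power with n = 10 on the stated inputs (paired test).**

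| True change | Power |
|---|---|
| 1.31% | 15% |
| 1.58% | 19% |
| 2.07% | 29% |
| 2.99% | 53% |
| 3.24% | 60% |
| 4.12% | 80% |

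A true change of 2.07% would need about 34 astronauts for 80% power.

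**The case against.** The strongest case on the other side has four parts.

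*The article never says how the interval was made.* It could be read as a sensitivity range over r, not as a confidence interval for the detectable difference. That r alone was moved is indeed an inference, but it rests on both limits agreeing to two decimals. The figure is labelled a 95% CI, and under that label the recipe is wrong.

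*Over-coverage is conservative, so an interval that is too wide does no harm.* A reader might infer this, or might conclude that the study is more precise than stated. The calculation does not support it. The interval is too wide only relative to its own centre. Against the paired result it is too narrow in points (1.93 against 2.80), and its upper end of 3.24% lies below the paired point value of 4.12%. Both ends are too optimistic, not only the favourable one.

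*Most of the false optimism comes from the factor of 2.* This stands. Changing the recipe alone moves the lower end from 1.31% to 1.58%, where power is still only about 19%. The interval method is the smaller of the two faults. It does not disappear once the centre is corrected, however: doubling the printed limits gives 2.62–6.48%, against 3.15–5.95%.

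*No decision depends on the figure.* This also stands in part. The article says that the number of astronauts available is limited, and nothing in its Statistical analysis section uses the interval. The consequence is confined to the sensitivity that the study claims.

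**Conclusion.** The concern holds as a joint error in one sentence. The interval comes from varying the correlation with the SD fixed. It over-covers (about 98.6%), and its relative width is too large by 37% in percentage points on the printed centre, or 42% in log-width; the 42% should not be quoted as if it were in points. The centre is Cohen's f times SD over mean, half of the paired detectable difference. On the published inputs the statement should read about 4.12% (3.15–5.95%).

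A reader might go further and conclude that 10 astronauts is the wrong number or that the planned test is invalid. The document does not support either. The n is presented as limited by availability, and a pre/post within-subject test suits the question.

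The figures assume equal SDs at both sessions, normally distributed differences, 20 df from the 21 pairs, and the mean of 2.01 cm³ treated as fixed. The actual SD of the paired differences is not published, so the corrected values may shift somewhat once it is used. The factors 0.765 and 1.444 would not, provided that all 21 pairs are used.

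**What to change.** From the earlier data, compute the SD of the 21 paired differences in average cervical disc volume directly. Put it and its chi-square 95% limits (20 df) through the paired formula, detectable difference = 0.996 × SD of differences for n = 10, and express the results as a percentage of the mean. Do not derive the interval from the confidence limits of r.

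Replace the point value and the interval together. Changing the interval alone would leave one of two faulty statements: 2.07% (1.58–2.99%), which makes the unfavourable end look better although power at 2.99% is about 53%; or 3.15–5.95% beside a point value that it does not contain. It would also help to say in one clause that the figure is the pre/post difference and that the interval reflects the uncertainty in the SD of the differences.

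The cost is a short recalculation, if the team still has access to the paired data it used here, and one corrected sentence. The planned number of astronauts, the measurements and the analysis stay as they are; the stated sensitivity becomes less favourable.
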